
## 2. Methods

### 2.1. Objectives

The main objective of this trial is to investigate the feasibility of adding a mentalization-based integrative team approach (MB-TA) to the EPP to better capture the risk of maltreatment among hard-to-reach clients in the existing EPP. EPP staff will be trained according to the MBT approach and regularly receive mentalization-based team supervision by a trained and experienced child and adolescent psychiatrist. The aim is to support staff in developing a more empathetic and consistent approach to challenging clients to keep them in the care program and thus reduce the risk of child abuse, maltreatment, and neglect. We hypothesize that the risk of maltreatment can be reduced by strengthening the competencies of professionals in the primary care system. This will be evaluated at the end of the follow-up period by comparing the subjects’ burden associated with the care for their child (measured by the Parental Stress Index scores) pre- and postintervention.

Secondary objectives:

The secondary objective is to investigate the modulating role of parental history of ELM in treatment success. This will be evaluated by analyzing the association between ELM (measured by the childhood experience of care and abuse questionnaire, CECA.Q) and the values on the primary outcome (Parental Stress Index).

Moreover, the feasibility of the approach will be investigated based on the acceptance of the intervention by staff members and their subjective feelings about the associated additional workload. This will be evaluated by measuring staff stress levels (using the trier inventory for chronic stress and a burden questionnaire) and staff metallization abilities (using the AMBIT service evaluation questionnaire).

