### 2.2. Study Design

The current trial is a single-center, non-randomized, open-label, single-arm feasibility study, including two local EPP teams in the wider area of Aachen, Germany. It is part of a larger consortium (the UBICA-II study), including an MBT-based intervention trial for psychiatric patients who are parents [34]. A total of at least 84 families in the care of the EPP will be systematically assessed at three time points: at the beginning of support from the welfare system (preintervention; T0), when support ends (postintervention; T1), and when the child is 12, 18, 24, or 30 months old, depending on their age at the time of inclusion in the study (follow-up; T2). The trial was approved by the local Research Ethics Committee at the University Hospital RWTH Aachen (reference EK 221/19) and will be carried out in accordance with the Declaration of Helsinki. The study was registered at the German Clinical Trials Register (DRKS00022075 on 8 July 2020). The study protocol was adapted in 2020, when it turned out that, due to the COVID-19 pandemic, the originally planned non-randomized study design with the nonconcurrent recruitment of two groups (first, a control group receiving usual EPP support, followed by the training and subsequent recruitment of the EPP employees for the “EPP-plus” intervention (experimental condition)) would not lead to comparable group conditions. Thus, the study was modified to a non-randomized, single-arm feasibility study. The aims of the feasibility study were adapted and now include evaluating (1) the acceptance of the approach by the EPP staff, (2) the burden of the EPP staff, and (3) the success of the EPP staff to better retain hard-to-reach parents/caregivers in the care program, in addition to our measures for the risk of maltreatment by parents. We chose a non-randomized, single-group feasibility study design for the following reasons: the EPP support systems vary across Germany with respect to type, dose, and mode of interventions, professional backgrounds, frequency of supervision and networking of the team, and legal and financial situations. Thus, it is not possible to choose a (non-randomized) comparable concurrent control group from another geographical region. Due to the planned team intervention, the randomization of individual staff members or individual parent dyads would have been impossible. The possible alternative approach of a cluster-randomized controlled trial with randomized teams would have resulted in very large sample sizes, e.g., for an effect size of d = 0.4, we would need 26 clusters with approximately 30 families each (total of 780 families) or approximately 23 clusters with 50 families each (total 1180 families), with an expected intracluster correlation coefficient of 0.1, entailing huge costs and logistical efforts. Since neither the feasibility nor estimated effect sizes on parents have been investigated for this mentalization-based team approach before, our current study is a necessary first step before such a large cluster-randomized trial.

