### 2.6. Outcomes

The primary outcome variable is the change in the parent-reported Parental Stress Inventory (PSI, [36]) scores from pre- to postintervention. A high parental burden can be considered a risk factor for dysfunctional parenting behavior. The PSI is a well-established 48-item self-report questionnaire for caretakers and can be utilized as a screening tool for dysfunctional parent–child interactions [37]. Good psychometric properties have been reported for the EBI, with reliability scores ranging from α = 0.95 for the total score to α = 0.93/0.91 for the domain scores. The validity of the instrument has been examined in several studies that have reported substantial associations between EBI scores and various indicators of parental stress [37].

As secondary outcomes, more detailed assessments of the parent and children’s health, as well as parent–child interactions, will be conducted when the child is aged 12, 18, 24, or 30 months. Secondary parental outcomes are the total and subscale scores of the Adult & Adolescent Parenting Inventory (AAPI-2, [38]), parental health (Patient Health Questionnaire, PHQ, [39]), child abuse potential (Child Abuse Potential, CAPI, [40]) and the level of social support (Social Support Questionnaire, Fsozu, [41]). The internal consistency of the depression scale of the German PHQ is given as α = 0.88 [42]. The internal consistencies of the main scales and the total score of the FSozu are between α = 0.81 and α = 0.93 [41]. The reflective functioning of the parents will also be recorded before (T0) and after (T1) the intervention as well as during the follow-up (T2) using the Parental Reflective Functioning Questionnaire (PRFQ, [43]). Estimates of internal consistency were 0.70, 0.82, and 0.75 for the three subscales [43].

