### 2.7. Participant Timeline

The flow of participants from recruitment through the end of the study is shown in Figure 1. Children and primary caregivers will be systematically assessed at T0 (preintervention), shortly after the parent has agreed to participate in the study, and at the end of the intervention carried out by the EPP staff (T1, postintervention). The timing of T1, however, will be different for each subject since the duration of the intervention is not standardized but depends on the individual needs and wishes of the family. A follow-up assessment will take place when the child is 12, 18, 24, or 30 months old, depending on the age at first assessment. If the child is ≤4 months old when the EPP team first assists, the assessment will be carried out when the child is 12 months old (T2); if the child is already older than 4 months old, the assessment will be carried out when the child is 18 months old (T2); if the child is already older than 12 months, the assessment will be carried out when the child is 24 months old (T2); and if the child is already older than 18 months, the assessment will be carried out when the child is 30 months old (T2). In the preintervention period, an EPP employee will have visited families a maximum of 5 times (corresponding to T0). The end of the intervention is defined by the end of support by the EPP (corresponding to T1). Moderators of treatment outcomes and sociodemographic data will be assessed at T0. Participants will be paid EUR 50 for each assessment session.

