### 2.8. Sample Size

In the current study, we will analyze whether there is a statistically significant change in the primary outcome (PSI score for each parent) from T0 (preintervention) to T2 (follow-up assessment, paired comparison). With a sample size of 67 parents (with data at both time points), a power of 80% can be achieved (two-sided significance level of 0.05; one-sample t-test) for an effect of at least d = 0.35 (standardized difference in the mean; calculated with G * Power 3.1.9.6). Effects of this magnitude were observed for an MBT team approach in mothers (Suchman et al., 2013, moderate effects on caregiving behavior and child behaviors (d > 0.2), [57]) and are therefore also expected for the new “EPP-plus” approach. Taking into account a loss to follow-up rate of up to 20% (missing values in the primary outcome measure at FU), at least 84 study participants should be recruited.

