### 2.12. Statistical Methods for Primary and Secondary Outcomes

The effects of the “EPP-plus” are assessed in a pre-post comparison using the PSI scores with a one-sample t-test with a two-sided significance level of 5%. The primary analysis is based on the intention-to-treat (ITT) principle, which aims to include all subjects enrolled in the feasibility study. The analysis of the secondary results is carried out analogously. Exploratory analyses will investigate which family-level risk factors are associated with the magnitude of change in PSI, using linear models and considering the presence of socioeconomic disadvantage (e.g., unemployment, overall socioeconomic status), mental risk characteristics (e.g., mental/physical health, domestic violence), teenage motherhood, immigrant status, parental ELM (assessed by CECA-Q), AAPI-2 pre-intervention total score, age and gender (of parent and child), and child responsiveness (Infant Care Index).

The feasibility of the “EPP-plus” approach will be analyzed descriptively, using frequencies and proportions for nominal or ordinal variables or medians and interquartile ranges for quantitative variables. For feasibility, we will consider the median number of visits per family, the number of supervision sessions, and attendance by the EPP staff to supervision sessions. In addition, acceptance of the “EPP-plus” approach by the staff members and their work-related stress levels will be analyzed at the start, midterm, and end of the trial by linear mixed models accounting for the clustering of team members. Furthermore, potential staff- and team-related factors contributing to the outcome of the “EPP-plus” approach (such as job experience, professional background, etc.) will be analyzed.

All safety data, including adverse events, are analyzed descriptively in the Safety Population (SP), which includes all families who were visited at least once by a team member of the “EPP-plus” team.

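### The primary PSI contrast is stated inconsistently: section 2.6, by the protocol's own labels, means T0 to T1, while section 2.8 tests and powers T0 to T2

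*Protocol article*

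**What the plan says.** Section 2.6 (Outcomes) defines the primary endpoint: "The primary outcome variable is the change in the parent-reported Parental Stress Inventory (PSI, [36]) scores from pre- to postintervention". It gives no T-number, but the labels are set elsewhere. Section 2.2 lists the later assessments as "when support ends (postintervention; T1), and when the child is 12, 18, 24, or 30 months old", the second of these being the follow-up, T2. Section 2.7 places an assessment "at the end of the intervention carried out by the EPP staff (T1, postintervention". Section 2.5.1 also equates the end of EPP support with T1.

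Section 2.8 (Sample Size) says the study will look for a "statistically significant change in the primary outcome (PSI score for each parent) from T0 (preintervention) to T2 (follow-up assessment, paired comparison", and places the 20% loss at follow-up.

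The other places do not settle the matter. In section 2.1 the hypothesis is followed by "This will be evaluated at the end of the follow-up period by comparing" PSI scores, yet the same sentence calls the comparison pre- and postintervention; the abstract does the same. Section 2.12 says the effects "are assessed in a pre-post comparison using the PSI scores with a one-sample t-test with a two-sided significance level of 5" per cent, with no time point. Table 2 schedules the PSI at T0, T1 and T2.

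**The concern.** A primary outcome needs one variable at one time. Here the section that defines the outcome and the section that sizes the test for it point to different assessments, and the analysis section does not choose between them. Both contrasts will be available in the data.

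They are not interchangeable. On T1, section 2.7 says: "The timing of T1, however, will be different for each subject since the duration of the intervention is not standardized". T1 is therefore tied to when each family's support ends. T2 is tied to the child's age (12, 18, 24 or 30 months). A T0 to T1 change describes families as they leave support; a T0 to T2 change describes them at a set developmental point, whatever the length of support. No maximum duration of support is stated, so for a family still in care T2 could even come before T1.

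Two things are at stake. The power statement and loss allowance were made for T2, so an analysis at T1 would have no stated justification for either. And if the text were left as it is, this document could not show that the contrast reported as primary was chosen independently of the results.

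**Working it through.** **Step 1. What each section implies**

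| Place | Wording on the primary PSI contrast | Implied contrast |
|---|---|---|
| 2.6 | pre- to postintervention | T0 to T1, by the labels in 2.2, 2.5.1 and 2.7 |
| 2.8 | named time points; loss counted at follow-up | T0 to T2 |
| Abstract, 2.1 | evaluated when follow-up finishes, but called pre- and postintervention | mixed |
| 2.12 | pre-post only | not stated |
| Table 2 | PSI at T0, T1, T2 | both can be computed |

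Within 2.6 the same labels are used for the parental reflective functioning questionnaire: before is T0, after is T1, and follow-up is listed separately as T2. So 2.6 read on its own terms also gives T0 to T1.

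**Step 2. Reproduce the sample size in 2.8**

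Inputs from 2.8: d = 0.35, two-sided α = 0.05, one-sample t-test on the paired change, power 80%, loss 20%.

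Power = P(|t| > t(0.975, n−1)), where t is noncentral with n−1 degrees of freedom and noncentrality d√n.

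- n = 66: power 0.7999
- n = 67: noncentrality 0.35 × √67 = 2.86, power 0.806

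The smallest n reaching 80% is 67, as stated. (The normal approximation, ((1.960 + 0.842)/0.35)² = 64.1, gives 65.) Recruitment: 67 / (1 − 0.20) = 83.75, rounded up to 84, as stated.

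The arithmetic is sound, and 2.8 attaches it to T2. Naming one time point leaves 67 and 84 unchanged for the same d and loss. The article gives no separate effect size or loss rate for T1.

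**Step 3. Worst case if the choice stayed open**

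Suppose either contrast could be called primary, each tested at two-sided 5%, with no true change at either time. Then

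P(at least one significant) = 1 − P(|Z₁| < 1.96 and |Z₂| < 1.96),

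with (Z₁, Z₂) bivariate normal with correlation r. The documents give no r, so a range is assumed:

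| r | P(at least one significant) |
|---|---|
| 0 | 1 − 0.95² = 9.75% |
| 0.3 | 9.5% |
| 0.5 | 9.1% |
| 0.7 | 8.3% |
| 0.9 | 7.0% |

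The two changes share the T0 score. If the three PSI scores have equal variance σ² and equal pairwise correlation ρ, the changes have covariance σ²(1 − ρ) and variance 2σ²(1 − ρ) each, so r = 0.5 whatever ρ is. That makes 9.1% a natural reference value and r = 0.3 a low assumption.

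**Step 4. What it would cost to test both formally**

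With α = 0.025 for each contrast, power at n = 67 and d = 0.35 falls to 71.5% per test. Restoring 80% needs 81 evaluable; 81 / 0.80 = 101.25, so 102 recruited. Choosing one time point avoids this.

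**The case against.** The best defence is that the text, taken as a whole, already leans to T2. Section 2.8 is the only sentence that states the primary test with time points, and it says T0 to T2. The abstract and 2.1 put the evaluation at the close of follow-up. The abstract describes T1 as an interim measurement. Section 2.9 plans drop-out to a one-year follow-up. Section 2.6 never prints T1; that reading comes from the protocol's labels. On this view 2.6 is loose wording. This stands as to intent: the two readings are not equally supported. It does not remove the conflict, because 2.6 is where the primary outcome is defined, its words have an assigned meaning in this protocol, and 2.12 does not correct it.

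A reader might infer more than the documents support:

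- **That a confirmatory test is undefined.** The article calls this a feasibility study and leaves effectiveness to later randomized trials. It does have one primary outcome, a two-sided 5% test and 80% power, so the definition matters, but no decision rule hangs on it.
- **That the plan's error rate is about 9%.** No section allows success at either time. The figures in Step 3 are a worst case under assumed correlations.
- **That T1 will fall within about three months.** The 69% who stayed less than three months is a pre-study figure, and better retention is an aim of the intervention.
- **That the choice between total and domain PSI scores is also open.** Section 2.6 mentions domain scores only when reporting reliability. Naming the score is detail that an article may leave to the analysis plan.
- **That the registration is wrong or that nothing else fixes the time point.** Neither the registry entry nor an analysis plan is at hand, and either may already name T2.

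**Conclusion.** The point holds as an internal inconsistency in the definition of the primary outcome. As written, 2.6 gives T0 to T1 and 2.8 gives T0 to T2; T2 is the better-supported reading. The stated sample size is correct and needs no revision, but it and the loss allowance support T2 only. If the choice were truly left open, the false-positive rate could rise from 5% to between 7.0% and 9.5% for correlations of 0.9 down to 0.3. That range rests on the assumed correlations and on a rule of counting either contrast, which the plan does not state. The practical consequence is that the article alone does not fix which of two substantively different contrasts is primary.

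**What to change.** In the abstract and sections 2.1, 2.6 and 2.12, state the primary outcome as the change in PSI from T0 to T2, matching 2.8. List the T0 to T1 change as secondary. In 2.12, replace the bare pre-post wording with the named time points. Make and date the correction before the data are analysed.

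The cost is a wording change in four places. The PSI is already scheduled at all three assessments, so no new data are needed, and 67 evaluable and 84 recruited stay as they are. The registration and any analysis plan should be checked for agreement; whether they need changing cannot be judged from the article.

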### 2.7. Participant Timeline

The flow of participants from recruitment through the end of the study is shown in Figure 1. Children and primary caregivers will be systematically assessed at T0 (preintervention), shortly after the parent has agreed to participate in the study, and at the end of the intervention carried out by the EPP staff (T1, postintervention). The timing of T1, however, will be different for each subject since the duration of the intervention is not standardized but depends on the individual needs and wishes of the family. A follow-up assessment will take place when the child is 12, 18, 24, or 30 months old, depending on the age at first assessment. If the child is ≤4 months old when the EPP team first assists, the assessment will be carried out when the child is 12 months old (T2); if the child is already older than 4 months old, the assessment will be carried out when the child is 18 months old (T2); if the child is already older than 12 months, the assessment will be carried out when the child is 24 months old (T2); and if the child is already older than 18 months, the assessment will be carried out when the child is 30 months old (T2). In the preintervention period, an EPP employee will have visited families a maximum of 5 times (corresponding to T0). The end of the intervention is defined by the end of support by the EPP (corresponding to T1). Moderators of treatment outcomes and sociodemographic data will be assessed at T0. Participants will be paid EUR 50 for each assessment session.

### 2.8. Sample Size

In the current study, we will analyze whether there is a statistically significant change in the primary outcome (PSI score for each parent) from T0 (preintervention) to T2 (follow-up assessment, paired comparison). With a sample size of 67 parents (with data at both time points), a power of 80% can be achieved (two-sided significance level of 0.05; one-sample t-test) for an effect of at least d = 0.35 (standardized difference in the mean; calculated with G * Power 3.1.9.6). Effects of this magnitude were observed for an MBT team approach in mothers (Suchman et al., 2013, moderate effects on caregiving behavior and child behaviors (d > 0.2), [57]) and are therefore also expected for the new “EPP-plus” approach. Taking into account a loss to follow-up rate of up to 20% (missing values in the primary outcome measure at FU), at least 84 study participants should be recruited.

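### The 80% power in section 2.8 is correct arithmetic on an effect size the protocol does not support, and both it and the primary t-test assume independent families from two teams

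*Protocol article*

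**What the plan says.** Section 2.8 (Sample Size) tests the change in PSI from T0 to T2. "With a sample size of 67 parents (with data at both time points"), it says "a power of 80% can be achieved" ("two-sided significance level of 0.05; one-sample t-test") "for an effect of at least d = 0.35". The recruitment target of 84 allows for up to 20% loss to follow-up.

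The choice of d is justified by one sentence: "Effects of this magnitude were observed for an MBT team approach in mothers", followed in brackets by "moderate effects on caregiving behavior and child behaviors (d > 0.2"). Section 2.2 (Study Design) states that effect sizes on parents have not been investigated before for this team approach.

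On clustering, section 2.2 explains that a trial randomizing teams would need a very large sample, "with an expected intracluster correlation coefficient of 0.1". The study itself takes families from two teams. Section 2.12 specifies a one-sample t-test for PSI with no team or worker term. Clustering appears there only for staff acceptance and stress, which are analysed "by linear mixed models accounting for the clustering of team members".

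**The concern.** There are two separate weaknesses, both in what goes into the calculation.

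**Effect size.** The text presents 0.35 as already observed, but the only figure offered is that effects exceeded 0.2, on caregiving and child behaviour. The primary outcome is parent-reported stress. A lower bound on other outcomes is compatible with 0.35 but does not support it. There is also a question of scale. In a one-sample test on change, d is the mean change divided by the SD of the change. The protocol calls it only a standardized difference in the mean and does not say on which scale the cited effects were expressed.

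**Independence.** The intervention works through staff who are trained and supervised as teams, and each worker may look after several families. If PSI change is correlated among families of the same worker, the plain t-test understates its standard error. The confidence interval is then too narrow and the real type I error exceeds 5%. In an uncontrolled study whose result would inform a decision on a larger trial, a falsely significant improvement is the costly error.

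**Working it through.** **1. The protocol's own figure.** Inputs from section 2.8: n = 67, d = 0.35, two-sided alpha 0.05, one-sample t-test, 20% loss. Power comes from the noncentral t distribution with noncentrality d√n and n − 1 degrees of freedom.

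- Noncentrality 0.35 × √67 = 2.86, df 66: power 80.6%. The smallest n reaching 80% is 67.
- 67 / 0.8 = 83.75, rounded up to 84.

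Both figures reproduce.

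**2. Power at smaller effects, families independent, n = 67.**

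| d (mean change / SD of change) | Power with 67 pairs | Pairs needed for 80% | Recruited at 20% loss |
|---|---|---|---|
| 0.35 | 80.6% | 67 | 84 |
| 0.30 | 68% | 90 | 113 |
| 0.25 | 52% | 128 | 160 |
| 0.20 | 36% | 199 | 249 |

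The last row is the power at the quoted lower bound. It is not a best estimate.

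**3. Scale of d.** With equal variances at T0 and T2 and pre-post correlation r, the SD of change is SD × √(2(1 − r)). An effect on the raw-score scale therefore equals the d of the t-test only when √(2(1 − r)) = 1, that is, r = 0.5. The document does not give r.

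**4. What the ICC of 0.1 refers to.** For d = 0.4, 80% power and individual randomization, 99 families per arm are needed. With 30 families per team the design effect is 1 + 29 × 0.1 = 3.9, so 2 × 99 × 3.9 = 772 families, or 25.7 teams. This matches the 26 clusters in section 2.2. The 0.1 is thus a team-level value used to size a two-arm trial. It is not an ICC of change and not a worker-level ICC.

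**5. Sensitivity to worker clustering (assumed inputs).** The document gives no staff number and no ICC of PSI change. Assume k = 8 to 16 workers with equal caseloads and an ICC of change of 0.02 to 0.10. Then:

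- design effect DE = 1 + (67/k − 1) × ICC
- effective n = 67 / DE, with power at d = 0.35 taken from the noncentral t on that n
- type I error of the unadjusted test ≈ 2 × (1 − Φ(1.96/√DE))

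| k | ICC of change | DE | Effective n | Power at d = 0.35 | Type I error of plain t-test |
|---|---|---|---|---|---|
| 16 | 0.02 | 1.06 | 63.0 | 78% | 5.7% |
| 16 | 0.10 | 1.32 | 50.8 | 69% | 8.8% |
| 8 | 0.02 | 1.15 | 58.4 | 75% | 6.7% |
| 8 | 0.10 | 1.74 | 38.6 | 56% | 13.7% |

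These are approximations. A test using degrees of freedom based on the number of workers would have somewhat less power.

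**6. Teams as a random sample.** With two teams of 33.5 families and ICC 0.1, DE = 1 + 32.5 × 0.1 = 4.25, effective n = 15.8 and power about 26%. This applies only if the two teams stand for a population of teams.

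**The case against.** The strongest reply is that section 2.8 states power conditionally, for an effect of at least 0.35, and that statement is true under independence. A lower bound of 0.2 does not contradict 0.35. This stands. It leaves untouched the sentence claiming that effects of this size were observed, which nothing in the document shows.

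A reader might infer that the protocol's own ICC reduces its power to 26%, or that worker-level losses follow from its own figures. Neither is supported. The 0.1 belongs to teams and to a different design. Stable differences in PSI level between teams or workers cancel in a change score, so the ICC of change may be smaller. If inference is limited to these two teams, between-team variance does not inflate the standard error in this way and the 26% falls away.

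It would also be too strong to say that modelling clustering for staff outcomes shows the protocol recognised family clustering and then ignored it. Staff are measured three times and sit within teams, which is reason enough for a mixed model there. Section 2.12 also plans to examine staff- and team-related factors in the outcome.

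Two further replies carry less weight. One is that a cluster term could be left to the analysis plan. But the protocol names the primary test and sizes the study on it, so this is a stated choice. The other is that this is a feasibility study which defers effectiveness to randomized trials. That limits how much depends on the test, but section 2.8 still claims 80% power for a two-sided 5% test.

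**Conclusion.** The point holds in a limited form. The 67, 84 and 80% are computed correctly. The document does not support d = 0.35 for PSI change, and under independence power ranges from 81% at 0.35 to 36% at 0.2. Independence of families is assumed without discussion in both section 2.8 and section 2.12, although families share workers within two teams.

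The direction of the clustering effect is clear: any positive ICC of PSI change lowers power below 80.6% and raises type I error above 5%. Its size is unknown. The ranges of 56% to 78% power and about 6% to 14% type I error depend entirely on the assumed 8 to 16 workers, the assumed ICC of change of 0.02 to 0.10, and equal caseloads. The design does not need to change. The stated power and the primary analysis do.

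**What to change.** **Section 2.12.** State that inference is conditional on these two teams. Analyse PSI change with team as a fixed effect, coded so that the intercept is the mean change over both teams, and the main responsible EPP worker as a random intercept. Worker-clustered standard errors are an alternative. Use small-sample degrees of freedom in either case. This requires that one main worker can be identified for each family. Section 2.5.3 says staff fill in the visit logs but not that each family has a single worker, so this must be checked first.

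**Section 2.8.** Remove the claim that effects of this magnitude were observed. Define d as mean change over SD of change. Give power with 67 pairs under independence as 81% at d = 0.35, 68% at 0.30, 52% at 0.25 and 36% at 0.2. Add a clustering range labelled as assumption, for example 56% to 78% at d = 0.35 for 8 to 16 workers and an ICC of change of 0.02 to 0.10, with the actual staff number substituted once known. Omit the two-team figure of 26%, or show it only as the case in which teams are a random sample.

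**Cost.** Changes of wording and analysis, with no extra families. The stated power becomes less favourable and the confidence interval may be slightly wider.
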